### Objectives

The primary aim of this study is to evaluate the efficacy of Metaverse virtual support groups in improving the overall well-being of Ukrainian refugees. Secondary objectives include (1) understanding how virtual spaces impact Ukrainian refugees perceived social support and (2) whether such platforms can increase awareness of gender-based violence.

We aim to examine whether the eventual improvements observed in the active intervention groups are attributable to the interventions themselves rather than simply the passage of time. Therefore, we will compare the outcomes not only between the active intervention conditions but also with the waitlist control group, who are assessed similarly to the other groups but do not receive any intervention.

This study is critical in the current landscape for several reasons. Firstly, the metaverse offers a scalable way to reach a larger population of refugees who may be dispersed across various geographical locations, breaking the barriers of distance and time. Secondly, the anonymity provided by virtual environments may encourage more open dialogue about sensitive or stigmatizing issues, potentially leading to disclosures on sensitive topics and more effective emotional support and coping strategies. Lastly, utilizing immersive technology allows for a culturally and linguistically tailored approach, providing refugees not just with generic aid but with nuanced, community-specific support.

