### Trial design

This protocol outlines a randomized clinical trial conducted to assess the efficacy of virtual support groups (i.e., groups meeting in the Metaverse) for Ukrainian refugees. The participants are randomly assigned to one of three conditions: (1) In-Person intervention group; (2) Metaverse intervention group; and (3) Waitlist. Stratification will consider factors such as age, gender, and trauma, to achieve balanced group distributions.

Major assessments are at baseline, mid-intervention, post-intervention, and 3-month follow-ups.

Our trial follows an equivalence framework and has a 1:1 allocation ratio, meaning participants are evenly distributed between the intervention and control groups.

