### Outcomes and measures

#### Primary outcomes

The primary outcomes are the levels of depressive symptomatology and anxiety. We assess these outcomes by measuring changes in the total score from baseline to post-intervention. Specifically, we evaluate changes in the total scores of standardized assessment tools for depression and anxiety administered at baseline and post-intervention assessments.

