#### Sample size

An a priori power analysis based on a medium effect size estimation [37, 38] indicated that a total of 45 participants are needed (planned main statistical test is ANOVA repeated measures, within-between interaction; *f* = 0.25; statistical power = 0.95; *α* error probability = 0.05; three groups, four main measurements (pre-intervention, mid-intervention, post-intervention, and follow-up). Power analysis was computed using the G*Power 3.1 program [39].

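### The designated main test, a three-arm by four-occasion interaction, can be significant without any Metaverse effect; no Metaverse contrast is named to carry the efficacy conclusion

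*Protocol article*

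**What the plan says.** The Objectives section of the protocol article states: "The primary aim of this study is to evaluate the efficacy of Metaverse virtual support groups". It adds that outcomes will be compared between the two active arms and with the waitlist, without ranking these comparisons. The Primary outcomes section fixes the time window for depression and anxiety: "We assess these outcomes by measuring changes in the total score from baseline to post-intervention".

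The Sample size section then says that the "planned main statistical test is ANOVA repeated measures, within-between interaction", with "three groups, four main measurements (pre-intervention, mid-intervention, post-intervention, and follow-up" and effect size f = 0.25, power 0.95 and alpha 0.05. On that basis it "indicated that a total of 45 participants are needed".

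The Data collection, management, analysis section describes a mixed model over three assessments up to post-treatment, a separate mixed model for the 3-month follow-up, repeated measures ANOVA where data are complete, and a Bonferroni or false discovery rate correction. It designates no contrast as primary. The Trial design section describes an equivalence framework and says the trial "has a 1:1 allocation ratio, meaning participants are evenly distributed between the intervention and control groups".

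**The concern.** The test called main and the question called primary differ in two ways.

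- **Arms.** The interaction's null is that all three arms have parallel profiles. In-Person is an active arm, and the Background cites evidence that such groups help refugees. That null can therefore be false whether or not Metaverse does anything.
- **Occasions.** The test spans four occasions. The primary outcomes use two of them, baseline and post-intervention.

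A significant main test would therefore leave the primary aim unanswered until someone chose which comparison to read. The document does not say which one decides. The 95% power quoted for the main test also says nothing direct about the chance of detecting a Metaverse effect.

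**Working it through.** **Inputs from the protocol article:** three groups, four measurements, f = 0.25, alpha 0.05, power 0.95, N = 45 (Sample size); even allocation (Trial design), taken as 15 per arm.

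**Assumptions, not stated in the document:** correlation between occasions r = 0.5, sphericity, SD 1 at each occasion, and an effect profile of 0, 0.5d, d, d over the four occasions. Dropout and clustering by support group are ignored.

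**1. Reproducing the plan's figure.**
Noncentrality = f² × N × 4 / (1 − r) = 0.0625 × 45 × 4 / 0.5 = 22.5.
Degrees of freedom: (3 − 1)(4 − 1) = 6 and (45 − 3)(4 − 1) = 126.
The noncentral F gives power 0.955. The smallest N reaching 0.95 is 44, which is 45 in equal arms. The stated 45 is reproduced. Other correlations do not give it: in equal arms, r = 0, 0.3 and 0.7 give 87, 63 and 30.

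**2. Noncentrality when only In-Person works and Metaverse equals Waitlist.**
The profile 0, 0.5, 1, 1 has mean 0.625 and sum of squared deviations 0.6875. The arm pattern 0, 1, 0 has sum of squared deviations 2/3.
Interaction sum of squares = 0.6875 × 2/3 × d² = 0.4583 d².
Noncentrality = 15 × 0.4583 d² / 0.5 = 13.75 d².

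| In-Person d | Noncentrality | Interaction rejects |
|---|---|---|
| 0.5 | 3.44 | 22% |
| 0.8 | 8.80 | 55% |
| 1.0 | 13.75 | 78% |
| 1.28 | 22.5 | about 95% (0.955) |

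The last row is the plan's own f = 0.25 arising wholly from In-Person: d = √(22.5 / 13.75) = 1.28.

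**3. Check by simulation.** In 20,000 trials per scenario, with four time courses each scaled to f = 0.25 and only In-Person effective, the interaction rejected in 95.2% to 95.9%. In the same trials a Metaverse-versus-Waitlist test of baseline-to-post change rejected in 4.9% to 5.2%. With no effect in any arm, the interaction rejected in 5.2%. At f = 0.25 its rejection rate was about the same (95% to 96%) whether Metaverse alone, In-Person alone or both worked. A rejection therefore does not identify the arm.

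**4. Power of the contrast the aim calls for, Metaverse versus Waitlist at post-intervention.**
SD of change = √(2(1 − 0.5)) = 1. Baseline-adjusted SD = √(1 − 0.5²) = 0.866.
Noncentrality of t = d / (SD × √(2/15)), using the pooled variance from three arms.

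| d | Change score | Baseline-adjusted |
|---|---|---|
| 0.5 | 1.37, power 27% | 1.58, power 34% |
| 0.8 | 2.19, power 57% | 2.53, power 70% |

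**The case against.** The strongest reply is that an omnibus test followed by corrected comparisons is conventional, and that the plan has the parts for it: the Objectives announce comparisons between active arms and with the waitlist, and the analysis section foresees a multiplicity correction. This stands in part. The comparisons are planned, and nothing says that a significant interaction will be read as Metaverse efficacy. A reader might infer that the trial will claim efficacy from the omnibus alone; the document does not say so. Leaving detail to an analysis plan does not settle the matter, though, because the article itself names a main test, and that test does not answer the primary question.

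Other stronger readings also fail:

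- **An inflated type I error.** With In-Person effective the omnibus null is false, so the 22% to 78% are power. No section states Metaverse equal to Waitlist as the formal null, and the equivalence wording leaves the hypothesis open.
- **Ninety-five percent as the typical case or a ceiling.** It needs an In-Person effect of about 1.28 SD with none from Metaverse, although both arms follow the same session protocol. Nor is it a bound, since a larger In-Person effect would exceed it.
- **A difference at follow-up alone triggering the main result.** This applies to the four-occasion test in the Sample size section, not to the three-assessment model in the analysis section.
- **A harmful Metaverse effect producing significance.** So would any two-sided test, including the contrast proposed below. That is a reason to fix the direction of reading, not a special defect of the interaction.

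**Conclusion.** The point holds as a mismatch between the designated main test and the stated aim. The sample size of 45 is not an arithmetic error: it reproduces at r = 0.5. What fails is the inference. With Metaverse identical to Waitlist, the main test is positive in about 22%, 55% or 78% of trials for In-Person d of 0.5, 0.8 or 1.0, and in about 95% if the planned effect comes wholly from In-Person. These rates depend on the assumed correlation, sphericity, time profile and 15 per arm. The logical gap does not. It would be too strong to say that the trial cannot address its aim, because the planned arm comparisons could do so; none of them has been made the test on which the conclusion rests.

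**What to change.** In the Sample size and the Data collection, management, analysis sections:

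- Name the Metaverse-versus-Waitlist contrast at post-intervention, adjusted for baseline and taken from the model fitted to all three arms, as the test on which the efficacy conclusion rests for PHQ-9 and GAD-7. Conclude efficacy only in the direction of lower symptoms.
- Report In-Person versus Waitlist and Metaverse versus In-Person as separate contrasts with confidence intervals, under the planned multiplicity correction.
- Keep the interaction as a supportive or gatekeeping result.
- Reconcile this with the equivalence framework in the Trial design section.
- State that the 95% power belongs to the interaction only, and give the contrast's own power from the second table above, which is before dropout, clustering and multiplicity.

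The contrast uses assessments already scheduled, and the fix requires no added enrolment. The cost is a visibly less favourable power statement.

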The improvement in the mental health and well-being scores within and between the groups will be examined using mixed-effects linear regression with a random intercept and slope over time (three assessments: baseline, after session 2, and post-treatment) and fixed effects for treatment assignment. The 3-month follow-up data will be analyzed using linear mixed effects model that incorporates random intercepts for participants and facilitators. Additionally, we may consider including random slopes for time if the data structure warrants it. If ICC analyses will indicate the presence of a hierarchical structure, we will proceed with conducting multilevel analyses. In addition, we will incorporate fixed effects for time and intervention condition and include any necessary covariates. We intend to perform longitudinal analyses in order to ascertain the long-term effects of the intervention. To evaluate changes in outcome measures from the initial measurement to each subsequent assessment, we plan to employ repeated measures ANOVA, where the data is complete, or mixed effects models, where data is incomplete. Moreover, we acknowledge that the linear mixed-effects model allows for the inclusion of covariates (we plan to control for demographics), and this flexibility makes it a robust alternative to repeated measures ANOVA, especially in complex datasets. The use of covariates was taken into account appropriately in the mixed-effects model, which is another reason we plan this approach when dealing with missing or incomplete data. The results of the other measures—demographic variables and therapeutic alliance as potential moderators and mediators—will be examined in an exploratory manner, utilizing regression models or mediation analyses. The error probability and the issue of multiple testing will be addressed either by employing the Bonferroni correction or the false discovery rate correction. Missing data—over 5%—will be handled with multiple imputation methods. Oversight and monitoring of the data collection process is conducted by the principal investigator and the project manager. Check-in regular meetings are held to review the progress of data collection, address any issues that may arise, and ensure compliance with the study protocol and ethical guidelines.

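### The 0.95 power is calculated for one test at alpha 0.05; with two primary outcomes and a Bonferroni correction, 45 participants give about 0.92 per outcome

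*Protocol article*

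**What the plan says.** Three statements in the protocol article bear on this.

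- **Sample size.** The calculation is for one test: "planned main statistical test is ANOVA repeated measures, within-between interaction". Its inputs are f = 0.25, "statistical power = 0.95", and "error probability = 0.05; three groups, four main measurements". The result: it "indicated that a total of 45 participants are needed". The section mentions neither a second primary outcome nor an adjusted alpha.
- **Primary outcomes.** There are two: "The primary outcomes are the levels of depressive symptomatology and anxiety", measured by PHQ-9 and GAD-7. The article gives no order of testing and no rule that both must succeed.
- **Data collection, management, analysis.** A correction is promised, but its type is left open: "the issue of multiple testing will be addressed either by employing the Bonferroni correction or the false discovery rate correction". The sentence does not say which tests form the family.

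**The concern.** A power figure belongs to a test at a given significance level. If each primary outcome is judged at a stricter level than the one used for sizing, the stated power is too high for the test that decides the outcome. Here the alpha in the Sample size section is the full 0.05 for one test, whereas Bonferroni, the first correction named, would give each of the two primary outcomes 0.025.

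The article states both the planning alpha and the error-control rule, so the mismatch does not arise from detail left to an analysis plan. What is at stake is the accuracy of a headline design figure: readers and funders will take 0.95 as the chance of detecting the planned effect on each primary outcome.

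**Working it through.** **Inputs from the Sample size section:** f = 0.25, k = 3 groups, m = 4 measurements, alpha = 0.05, target power 0.95, N = 45.

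**Assumed, because not stated:** correlation between repeated measures rho = 0.5; sphericity (epsilon = 1).

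**Formulas** (noncentral F test for the within-between interaction):

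- lambda = f² × N × m / (1 − rho)
- df1 = (k − 1)(m − 1)
- df2 = (N − k)(m − 1)
- power = P(noncentral F with df1, df2, lambda exceeds the critical F at alpha)

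**Step 1. Reproduce the plan's figure.**

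- lambda = 0.0625 × 45 × 4 / 0.5 = 22.5
- df1 = 2 × 3 = 6; df2 = 42 × 3 = 126
- At alpha 0.05, power = 0.9555. With equal arms, 42 participants give 0.9391, so 45 is the smallest total that reaches 0.95.

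The plan's figure reproduces.

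**Step 2. Bonferroni over the two primary outcomes.** Alpha per outcome = 0.05 / 2 = 0.025. Lambda and degrees of freedom are unchanged.

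- Power at N = 45: 0.9209, a fall of 0.9555 − 0.9209 = 0.0346.
- Type II error per outcome: 1 − 0.9555 = 0.0445 becomes 1 − 0.9209 = 0.0791, about 1.8 times as large.
- Smallest total with equal arms that restores 0.95: 51 (17 per arm), power 0.956.

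**Step 3. False discovery rate over the two primary outcomes** (Benjamini-Hochberg, outcomes treated as independent). An outcome is declared significant if its own p ≤ 0.025, or if both p-values are ≤ 0.05. So

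power per outcome = 0.9209 + (0.9555 − 0.9209) × P(other p ≤ 0.05)

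- Both outcomes respond: 0.9209 + 0.0346 × 0.9555 = 0.954
- Only one responds: 0.9209 + 0.0346 × 0.05 = 0.923

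**Step 4. Sensitivity to the assumed correlation, N = 45.**

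| rho | power at alpha 0.05 | power at alpha 0.025 | N for 0.95 at alpha 0.05 |
|---|---|---|---|
| 0.3 | 0.851 | 0.774 | 63 |
| 0.5 | 0.956 | 0.921 | 45 |
| 0.6 | 0.987 | 0.973 | 36 |

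Power is lower at 0.025 in every row. Of the three correlations, only 0.5 returns the plan's own 45.

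**The case against.** The strongest case on the other side has five parts.

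- **The family is not defined.** The correction sentence follows directly after the exploratory moderator and mediator analyses and might have been meant for those. This stands in part: the article does not say that the correction covers PHQ-9 and GAD-7. But it exempts nothing. If the two primary outcomes were each tested at an uncorrected 0.05, the familywise error would be 1 − 0.95² = 0.0975 under independence. Either reading needs a clarifying sentence.
- **False discovery rate control is an equal option.** This stands. If both outcomes respond, which is a natural planning case, power stays at about 0.95. A reader might infer that power is lost under every permitted correction; Step 3 shows that it is not.
- **The loss is small, and the unknown correlation matters more.** Both are true. A correlation of 0.55 would bring power at alpha 0.025 back to about 0.95. But the plan's 45 is itself the answer for 0.5, so 0.92 is the like-for-like comparison.
- **The calculation contains no error.** Correct: 45 is right for its stated inputs. The fault is that the alpha input ignores the correction promised elsewhere.
- **The described analyses differ from the sized test.** The primary outcomes are defined as change from baseline to post-intervention, and a mixed model over three assessments is also planned. That is a separate matter. The Sample size section calls the four-measurement ANOVA the main test, so its power should be stated at the alpha that will apply.

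A reader might also infer a larger shortfall by extending the family to the secondary outcomes or by adding dropout. The documents define no such wider family and give no dropout rate, so no figure for either is supported.

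**Conclusion.** The point holds in a limited form. The stated 0.95 is the power of one uncorrected test. Under Bonferroni over the two primary outcomes, 45 participants give about 0.92 per outcome, roughly 3.5 percentage points less and still above 0.90. Under the false discovery rate option it is about 0.95 or about 0.92, depending on whether both outcomes respond. So the unconditional statement of 0.95 is supported under only one of the two permitted corrections, and in one scenario.

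The figures rest on sphericity, on a correlation of 0.5 inferred from the plan's own total, on a family made up of the two primary outcomes and, for the false discovery rate figures, on independence between them. The direction does not depend on the correlation, but the size does. This is a correction worth making to a design figure. It does not show that the trial is badly underpowered.

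**What to change.** Two sentences need to change.

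1. In Data collection, management, analysis, state that the multiplicity correction for the primary analysis covers the two primary outcomes, PHQ-9 and GAD-7.
2. In Sample size, restate the power at the per-outcome level that follows, with the assumed correlation. For Bonferroni, for example: with 45 participants, power is about 0.92 for each primary outcome at alpha 0.025, assuming a correlation of 0.5 between repeated measures and sphericity. If the false discovery rate is kept instead, give both figures: about 0.95 if both outcomes respond and about 0.92 if only one does.

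The cost is a slightly less favourable power statement; the sample size need not change. If the sponsor prefers to keep 0.95 under Bonferroni, the same assumptions give 51 participants, six more than planned.

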#### Recruitment

Prospective participants are recruited into the study by research assistants working with NGOs focused on Ukrainian refugees.

Collaborations with local NGOs, including the Sensiblu Foundation and regional Refugee Centers based in Bucharest, Romania, facilitate the recruitment process. These organizations provide direct access to the target population through their networks and community engagement efforts. An initial telephone discussion screens those people who are motivated to participate in the study. The screening interview focuses on the exclusion criteria (age, involvement in any current therapy process, and mental health diagnoses). Social media venues as well as posters and fliers are also used for the recruitment process. Recruitment strategies include community outreach, digital engagement, and collaboration with NGOs. Continuous efforts are maintained to meet the sample size requirement, with provisions for extended recruitment if necessary.

#### Assignment to interventions

The participants are randomly assigned to one of the three conditions (Metaverse, In-Person, Waitlist) using a sequence generated by the software randomizer.org.

The process of random allocation is executed by the project manager employing a straightforward random sequence, assigning one of three distinct numbers to each participant—either 1, 2, or 3, based on the number of the experimental condition.

Participants are enrolled by the project manager and trained facilitators from partner NGOs, with eligibility confirmed through thorough screening assessments. The project manager independently assigns participants to intervention groups, and allocation concealment is maintained by storing allocation lists as password-protected documents, accessible only after baseline assessments, ensuring that both participants and recruiters remain blind to group assignments until the intervention begins.

The Metaverse and In-Person groups are facilitated by two different psychotherapists, trained in evidence-based psychotherapies and group interventions, and who have at least 1 year of experience working with refugees. Both psychotherapists follow the same protocol structure (described in the “Interventions” section) to deliver the intervention.

The principal investigator and the statisticians conducting the data analysis remain unaware of the experimental condition until the study concludes.

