### Participant timeline

Potential participants are assessed for eligibility through an initial assessment phase conducted by phone calls. If the inclusion criteria are met, written consent for participation in the study is obtained. After the initial assessment, the participants meeting the inclusion criteria are randomly assigned to one of the three conditions: (1) Metaverse Condition, (2) In-Person Condition, and (3) Waitlist condition (see flow diagram in Fig. 2). After the initial assessment, the subsequent measures consist of the instruments provided in the “Outcome measures” section. The participants are then randomized by a research assistant without being informed about their group allocation. A priori randomization is performed with a designated computer software (http://www.randomizer.org). Participants who do not meet the criteria for the study are referred to the appropriate entities and structures.

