### Trial status

Preregistration: https://clinicaltrials.gov/study/NCT06142032; protocol version: 2, 15.02.24. Participant recruitment started on December 20, 2023. Recruitment end (estimated): April 2024. Randomization of the participants was performed on December 15, 2023.

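### Allocation concealment is not assured as described: the project manager both enrols participants and runs the allocation, and the sections disagree on who randomizes

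*Protocol article*

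**What the plan says.** All references are to the protocol article.

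*Assignment to interventions* gives the project manager three tasks:

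- Running the sequence: "The process of random allocation is executed by the project manager employing a straightforward random sequence".
- Enrolling, together with facilitators: "Participants are enrolled by the project manager and trained facilitators from partner NGOs, with eligibility confirmed through thorough screening assessments".
- Assigning arms and relying on a stored list: "The project manager independently assigns participants to intervention groups, and allocation concealment is maintained by storing allocation lists as password-protected documents".

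The same sentence adds that the lists can be opened only once baseline assessments are done, and concludes that participants and recruiters are blind to assignment until the intervention begins. It does not name who knows the password, or say whose baseline must be complete.

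*Participant timeline* describes randomization as a priori and names a different person: "The participants are then randomized by a research assistant without being informed about their group allocation". *Recruitment* gives research assistants another role: "Prospective participants are recruited into the study by research assistants working with NGOs focused on Ukrainian refugees".

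*Trial status* says: "Randomization of the participants was performed on December 15, 2023". It puts the start of recruitment at 20 December 2023 and its estimated end in April 2024.

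**The concern.** Concealment means that whoever decides if and when a person enters the trial cannot know that person's arm beforehand. The protocol claims this, but describes an arrangement in which one person does both jobs. The competing account, with a research assistant randomizing, does not clearly separate them either.

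The arms differ in practical appeal: online access through a browser, attendance at an NGO office, or waiting. The primary outcomes, PHQ-9 and GAD-7, are self-reported. Someone who knew the next assignment could influence who enters and when. In a trial of 45 participants, a few steered entries could unbalance prognosis between arms in ways that were never measured.

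**Working it through.** The point concerns procedure and rests on no figure in the plan. The check sets the sections side by side.

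| Task | *Assignment to interventions* | *Participant timeline* | *Recruitment* |
|---|---|---|---|
| Recruit or enrol | Project manager and NGO facilitators | Person not named | Research assistants working with NGOs |
| Execute the randomization | Project manager | A research assistant | Not stated |
| Assign the arm | Project manager | A research assistant | Not stated |
| Hold the password | Not stated | Not stated | Not stated |

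**Step 1: roles within one section.** "Participants are enrolled by the project manager and trained facilitators from partner NGOs" and "The project manager independently assigns participants to intervention groups" stand in the same paragraph. The project manager is therefore one of the people who bring participants in, and also the one who allocates them. The claim that recruiters are blind cannot be true of that person. A password protects a list from others, not from the person who runs the sequence and makes the assignments.

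**Step 2: the other account.** If a research assistant randomizes, that contradicts step 1. It would restore concealment only if that assistant took no part in recruitment. The document does not say so.

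**Step 3: timing.** The inputs are:

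- The sequence is made in advance (*Participant timeline*).
- Baseline is done at enrolment, and the first session follows about 1 to 2 weeks later (*Participant timeline*).
- Groups begin to form once six people have enrolled (*Interventions*).
- Recruitment runs from 20 December 2023 to an estimated April 2024, about four months (*Trial status*).

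Two weeks is much shorter than four months. On the stated interval, someone in an intervention arm with baseline on 20 December 2023 would start by about 3 January 2024 (20 December plus 14 days). Recruitment would still have roughly three months to run. Early assignments are thus probably known while later people are being screened.

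**Step 4: when the lists open.** The wording allows three readings.

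- After each participant's own baseline: opening a single list may show later assignments too, unless they are released singly.
- After a batch's baselines, with a separate list per batch: later batches could stay hidden.
- After everyone's baseline: this fits poorly with the 1 to 2 week gap and rolling group formation.

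The overlap in step 1 remains under all three.

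**Step 5: size.** Any figure for bias or inflated type I error needs an assumed prognostic shift between arms. The document offers no basis for one, so none is given.

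**The case against.** The strongest reply is that the article condenses a fuller protocol, that custody of the password may be settled there, and that nothing shows anyone looked ahead. Most of this stands. It limits the point to assurance as described, but does not resolve two contradictions on the page: an enroller who allocates although recruiters are said to be blind, and two different people named as randomizer.

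A reader might infer several stronger things that the document does not support:

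- *The list opens after the first baseline, exposing every later assignment.* The text says neither. It speaks of lists and assessments in the plural, and the batch reading is possible.
- *An enroller allocates under either account.* The randomizing research assistant and the recruiting ones may be different people. What can be said is that separation is not stated.
- *Randomizing on 15 December, five days before recruitment opened, is itself a fault.* Generating a sequence beforehand is normal practice. The sentence in *Trial status* is only unclear, because it speaks of participants when recruitment had not begun.
- *Eligibility is loose enough to steer freely.* Most criteria are factual or score-based: age, formal diagnosis, current therapy, PTSD score. Imminent danger, in *Ethics and dissemination*, is the clear exception. As described, the sequence is simple, so past assignments do not predict the next; sight of the list would.
- *No analysis could help.* The primary outcomes are changes from baseline and demographic covariates are planned, so measured imbalance is partly handled. Unmeasured selection is not.

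Two other safeguards do not answer the point. Blinding the principal investigator and statisticians protects the analysis. Keeping the project manager out of the sessions protects delivery. Neither protects entry to the trial.

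**Conclusion.** The concern holds in this form: concealment is not assured as the protocol describes it. The role overlap in *Assignment to interventions* and its conflict with *Participant timeline* are read directly from the text. That early assignments are known during later screening is a probable inference; it assumes that groups start as they fill and that the 1 to 2 week gap is kept. That later assignments may be visible is conditional on their not being released one at a time.

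No actual breach is shown, and the size of any resulting bias cannot be estimated from the document. The case for acting rests on a small trial, self-reported outcomes, arms of differing appeal and a cheap remedy.

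**What to change.** 1. Remove the project manager from enrolment and eligibility decisions, since NGO facilitators already enrol. Alternatively, give the list to an existing team member who does not recruit.
2. Release one assignment at a time, by participant ID, after that person's consent, eligibility and baseline are complete.
3. Reconcile *Participant timeline*, *Recruitment* and *Assignment to interventions* on who generates, holds and releases the allocation.
4. Clarify in *Trial status* whether 15 December 2023 is the date the sequence was generated.
5. For participants already allocated, report who held the list and when it was opened. Recruitment began in December 2023 and protocol version 2 is dated 15 February 2024, so a change of roles cannot protect those who entered before it.

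The cost is a reassigned task among existing staff, a few corrected sentences, a short account of past practice, and a short delay before each assignment.
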